A sample training schedule is included (Table S2 in Multimedia Appendix 2), but this will be tailored based on participants’ progress. Supervision will take place until the participant is deemed independent. Participants will be asked to demonstrate all steps of the exercise regimen on the treadmill in the last supervised sessions before being deemed independent, and they will be asked to repeat this at each subsequent supervised session, taking place once a week over the duration of the study. All participants will be offered as much support as needed to successfully complete the exercise intervention. The study team will offer additional phone calls, supervised sessions, or in-person assistance at the research center. Video tutorials will be made available to all participants as guides for using the exercise equipment and for being able to visualize the resistance training exercise movement patterns.

Participants in the usual care control group will continue their baseline level of activity that they were doing prior to enrollment in the study and will be asked to complete physical activity logs to evaluate adherence. At the end of the randomization period, participants in the control group will be offered the chance to participate in the 26-week home-based, combined endurance and resistance training program.

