### Outcomes

#### Overview

The outcomes for EXCEL-PD are listed below as well as in Table 1, which includes the domain, measure, metric, method of aggregation, and time point for each outcome.

**Table 1. T1:** EXCEL-PD^a^ trial outcomes.

Outcome measure	Domain	Specific measurement variable	Metric	Method of aggregation	Time points
Primary outcomes					
Feasibility	Feasibility	Average % HRmax^b^ and RM^c^	Value at time point assessed	Mean, SD, median, range	Weeks 7‐26
Adherence	Adherence	Number of days exercised per week and duration at target intensity per session	Value at time point assessed	Mean, SD, median, range	Weeks 7‐26
Safety	Safety	Incidence of adverse events and serious adverse events	Number of events	Number and rate of events	Continuous
Secondary outcomes					
Global cognitive function	Cognitive function	Montreal Cognitive Assessment Scale	Score at time point assessed	Mean, SD, median, range	Screening and 26 weeks
MDS-UPDRS^d^ motor score (part III)	Motor sign assessment of Parkinson disease	MDS-UPDRS motor score (part III)	Score at time point assessed	Mean, SD, median, range	Baseline and 26 weeks
Klotho	Neuroendocrine	Klotho protein (nm/L)	Value at time point assessed	Mean, SD, median, range	Baseline and 26 weeks
Cortisol	Neuroendocrine	Cortisol hormone (pg/mL)	Value at time point assessed	Mean, SD, median, range	Baseline and 26 weeks
Brain-derived neurotrophic factor	Neurotrophic	BDNF^e^ protein (pg/mL)	Value at time point assessed	Mean, SD, median, range	Baseline and 26 weeks
C-reactive protein	Inflammation	CRP^f^ protein (mg/L)	Value at time point assessed	Mean, SD, median, range	Baseline and 26 weeks
Exploratory outcomes					
Domain-specific cognitive function	Cognitive function	Trail Making Test, Alternating Verbal Fluency, and NIH^g^ Toolbox	Score at time point assessed	Mean, SD, median, range	Baseline and 26 weeks
Six-minute walk	Functional capacity	Distance walked in 6 minutes in meters	Value at time point assessed	Mean, SD, median, range	Baseline and 26 weeks
VO2peak^h^	Cardiorespiratory fitness	Peak volume of oxygen consumed	Value at time point assessed	Mean, SD, median, range	Baseline and 26 weeks
Hand grip and knee extensor strength	Strength	Maximum strength (kg)	Value at time point assessed	Mean, SD, median, range	Baseline and 26 weeks

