#### Primary Outcomes

The primary outcomes for the study are feasibility, adherence, and safety of the combined exercise intervention. Adherence and feasibility will only be evaluated in the exercise group. Feasibility will be measured using the average percentage of HRmax for endurance exercise sessions and the average repetition maximum for resistance exercise sessions. Adherence will be measured using the average number of days exercised per week, the duration of exercise for resistance exercise, and the duration of exercise at target HR intensity for endurance exercise. Participants will keep track of exercise sessions using exercise diaries, which investigators will use to assess adherence. Data from Polar HR monitors will be used to assess feasibility. Safety will be measured by the incidence of adverse events (AEs) and serious AEs in the exercise and control groups.

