#### Blinding

Due to the nature of the intervention, trial participants are not blinded to their study intervention group (exercise vs waitlist control). The investigator completing the assessments is also not blinded, as the same investigator is needed to monitor safety and adherence.

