#### Statistical Methods for Primary and Secondary Outcomes

The primary outcomes are feasibility, adherence, and safety of the combined exercise program. To assess feasibility, we will estimate the overall average %HRmax for endurance training and average repetition maximum for resistance training and their corresponding 95% CIs for the exercise group at 26 weeks. We will then compare the average to the intended target intensity (82.5% for endurance exercise and 10-RM for resistance training) using a 1-sample *t* test (*α*=.05). We will use repeated measures ANOVA of weekly %HRmax and linear mixed models to assess any trends over time from weeks 7 to 26, including a random effect for time within participant as sample size permits. To measure adherence in the exercise group, the average number of days per week exercised and the duration of time (minutes) exercised at the specified intensity will be calculated. Achievement of the adherence (hypothesized to be at least 3 d/wk) will be tested using 1-sided, 1-sample Student independent group *t* tests. To assess safety, the incidence of individual AEs (including serious AEs) and exact CIs will be calculated. We will use Fisher exact or Poisson exact tests to compare exercise and control groups for AEs that are definitely, probably, or possibly related to the exercise intervention as categorical variables.

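### The only between-group safety test counts adverse events related to an exercise programme that controls do not receive, so it does not test the primary safety outcome as defined

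*Protocol article*

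**What the plan says.** The Primary Outcomes section defines the endpoint without any causality filter: "Safety will be measured by the incidence of adverse events (AEs) and serious AEs in the exercise and control groups". Table 1 (Outcomes, Overview) agrees: "Incidence of adverse events and serious adverse events", summarised as the number and rate of events.

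The section Statistical Methods for Primary and Secondary Outcomes confirms the status of the endpoint ("The primary outcomes are feasibility, adherence, and safety of the combined exercise program") and then gives two safety analyses:

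- A descriptive one, with no relatedness filter: "To assess safety, the incidence of individual AEs (including serious AEs) and exact CIs will be calculated".
- A group test, by an exact method (Fisher or Poisson), whose stated purpose is this: "compare exercise and control groups for AEs that are definitely, probably, or possibly related to the exercise intervention as categorical variables".

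On exposure, Intervention and Comparator states: "Participants in the usual care control group will continue their baseline level of activity that they were doing prior to enrollment in the study". Controls are also asked not to increase their activity (Concomitant Care) and are offered the programme only after their final visit (Sequence Generation and Randomization).

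On who judges, the Blinding section states: "The investigator completing the assessments is also not blinded, as the same investigator is needed to monitor safety and adherence".

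**The concern.** A comparison of harms should set events under treatment against the background rate that the control group supplies. Here the event set is filtered by attribution to an exposure that only one arm has. The control group then supplies no background rate, and the test cannot separate harm caused by exercise from ordinary events that happen to be attributed to it.

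Two errors are possible within this test. Common minor complaints judged possibly related can produce a significant result with no true excess of AEs. Conversely, a real excess judged unrelated adds nothing to the test statistic. In both directions the result depends on causality judgements made with the allocation known. Because safety is a primary outcome, the only inferential statement about it should address the outcome as defined.

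**Working it through.** The protocol gives no AE rate, power or sample size for the safety comparison, so there is no figure of its own to reproduce. What follows is the behaviour of the planned test.

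**Inputs from the protocol.** 16 exercise and 15 control participants (Sample Size); two controls have withdrawn without a final visit (Recruitment and Retention), leaving 13 if no more are lost; Fisher exact or Poisson exact test. No significance level is stated for the safety test; two-sided 0.05 is assumed.

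**Step 1: the control cell.** No exercise intervention is given to controls during the comparison period, so a correctly coded control count of events related to it is 0.

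**Step 2: Fisher exact test, k of 16 against 0 of 15.** For k = 4, 5 and 6, the two-sided p-value is the probability of the two extreme tables, in which all k affected participants fall in one arm:

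p = [C(16,k) + C(15,k)] / C(31,k)

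- k=4: (1820 + 1365) / 31465 = 0.101
- k=5: (4368 + 3003) / 169911 = 0.043
- k=6: (8008 + 5005) / 736281 = 0.018

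With 13 controls, k=5 gives (4368 + 1287) / 118755 = 0.048. The threshold is therefore five exercisers with an attributed event, with either control count.

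**Step 3: Poisson exact test, equal follow-up per participant.** With all k events in the exercise arm, p = (16/31)^k + (15/31)^k. Five events give 0.063 and six give 0.032, so the threshold is six events.

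**Step 4: how often the test rejects when exercise causes no excess.** Let a proportion q of each arm have any AE, and let a fraction f of the exercisers with an AE have it judged at least possibly related. The Fisher test rejects when X ≥ 5, with X ~ Binomial(16, q·f). Both q and f are assumptions. The last column is the Fisher test on all AEs in both arms, by exact enumeration.

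| q | f=0.5 | f=0.8 | f=1.0 | All-AE test |
|---|---|---|---|---|
| 30% | 8% | 33% | 55% | 2.7% |
| 50% | 37% | 83% | 96% | 3.0% |
| 70% | 71% | 99% | 100% | 2.7% |

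**Step 5: what the all-AE test can detect.** Its power is 31% for 30% against 60% of participants with an AE, and 54% for 30% against 70%. It is valid but weak at this size.

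**The case against.** The strongest reply is that the sentence immediately before the test already plans unfiltered AE and SAE incidence with exact confidence intervals, in line with the outcome definition. The Harms section promises that all AEs will be published, and an independent safety monitor reviews AEs about every six months. This stands. A reader might infer that safety goes unassessed, or that harm judged unrelated disappears from the trial; the document does not support that. Such events are lost from the group test only.

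Second, no stopping rule, success criterion or stated alpha hangs on the test, and a spurious rejection would count against the programme. It would be wrong to infer that the trial could be falsely declared safe because of it. Nor is reducing falls a stated objective, so the test's inability to show such a benefit is not a failure of this plan.

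Third, the control zero is deduced from the design and is not stated. One could read relatedness as meaning the kinds of event that exercise might cause, such as strains or falls, which controls can also have. That would make the comparison coherent, but it is not what the sentence says. The Harms section ties its grading to the study as a whole, which control events from lumbar puncture or blood draws could meet; the analysis section uses the narrower exercise intervention. A control event coded as possibly related to exercise would be miscoding and would not supply a valid comparator.

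Fourth, the counts and rates in the working are hypothetical. That is true of Step 4. The thresholds in Steps 2 and 3 need only the group sizes, the zero control count and the assumed two-sided 0.05 level.

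**Conclusion.** Wrong as written, with a limited scope. The only between-group safety test uses an event set that the control arm cannot contribute to, and so does not test the primary safety outcome defined in Primary Outcomes and Table 1. In effect it asks whether at least five of 16 exercisers have an event that an unblinded investigator calls at least possibly related (p=0.043 at five, 0.018 at six). This rests on the planned group sizes, correct coding of control events, and a two-sided 0.05 level. How far the false-positive rate departs from nominal depends on AE and attribution rates that the protocol does not give; over the combinations tabulated it runs from 8% to 100%, against about 3% for the all-AE test.

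The defect is confined to that test. The planned incidence estimates cover all AEs and SAEs, but the article states no group comparison for them.

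**What to change.** Change the last sentence of the safety paragraph in Statistical Methods for Primary and Secondary Outcomes as follows:

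- Compare all AEs, and separately all SAEs, between groups over the 26 weeks regardless of attribution, both as participants with at least one event and as an event rate per person-time.
- Give the risk or rate difference with an exact 95% CI as the main result, with the Fisher or Poisson exact p-value as support.
- Report exercise-related AEs descriptively, with exact CIs, in the exercise arm only.
- Report specific event classes, such as falls or musculoskeletal events, descriptively by arm. A set of separate tests would be excessive for 31 participants.

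The cost is one amended sentence before analysis starts in June 2026. No new data are needed, since the Harms section already requires all harms to be documented. The downside is low power, so the text should call the comparison an estimate and should not read a non-significant result as evidence of equal safety.

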Secondary outcomes are changes from baseline in global cognitive function, motor function, and circulating biomarkers in both the exercise and control groups. Two-way repeated-measures ANOVA will be conducted to test for differences in MoCA from baseline to week 26 by group. Within each group, paired samples Student *t* tests will be conducted to test differences in MoCA from baseline to week 26. We will also examine a difference in differences analysis within and between groups overall using ANOVA. If data permit, we will use mixed-effects linear models, with time (baseline and week 26) and group (exercise and control) as the fixed effects and participant as the random effect within each model, to determine the association between change in MoCA and each of the following covariates separately to identify important differences: age, sex, education, disease duration, disease severity (defined by Hoehn and Yahr stage, MDS-UPDRS), and use of PD medications (calculated levodopa equivalent dose). Similar analysis will be performed as above to examine differences in MDS-UPDRS motor score (part III) and circulating biomarkers (neurotrophic: BDNF; inflammatory: CRP; neuroendocrine: klotho and cortisol) from baseline to week 26.

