### Methods for Additional Analyses

We will investigate several other outcomes and measures that may respond to exercise. These include participant-reported outcomes: MDS-UPDRS part II for nonmotor and motor aspects of experiences of daily living, PDQ-39 and PDAQ-15 for quality of life, PFS-16 for fatigue, and BDI-II, PAS, and AS for mood, and UCLA Loneliness Scale. We will expand cognitive analyses to evaluate changes in domain-specific functions. Using paper-based assessments (Trail Making Test and Alternating Verbal Fluency) and tablet-based assessments (NIH Toolbox), we will measure cognitive performance for each cognitive domain: executive function and working memory, processing speed and attention, visuospatial function, memory, and language. Changes from baseline in cardiorespiratory fitness (VO2peak), strength (maximal knee extension and handgrip strength), and functional capacity (6-minute walk) will also be assessed. Change in PGI-S from baseline, and Patient Global Impression of Change and Clinical Global Impression of Change will also be assessed.

Two-way repeated-measures ANOVA will be conducted to test for differences in each outcome from baseline to week 26 by group. Within each group, paired Student *t* tests will be conducted to test differences in outcome from baseline to week 26. We will use mixed-effects linear models, with time (baseline and week 26) and independent group Student *t* test (exercise and control) as the fixed effects and participant as a random effect within each model, to determine the association between change in outcome and each of the following covariates: age, sex, education, disease duration, disease severity (defined by Hoehn and Yahr stage), use of PD medications (calculated levodopa equivalent dose).

We will also collect an Exercise Attitudes, Beliefs, and Goals questionnaire at baseline and week 26. This questionnaire is designed to measure an individual’s attitudes and beliefs regarding exercise as well as confidence to continue exercising. Finally, collected blood, saliva, and CSF specimens may also be analyzed for changes in additional neurotrophic, inflammatory, and neuroendocrine biomarkers.

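### The pre/post outcomes get a valid but unadjusted change-score test plus paired t tests within each arm; a baseline-adjusted ANCOVA would use data already collected

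*Protocol article*

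**What the plan says.** Under Statistical Methods for Primary and Secondary Outcomes, the protocol article sets out four analyses of the Montreal Cognitive Assessment (MoCA):

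- a between-group test: "Two-way repeated-measures ANOVA will be conducted to test for differences in MoCA from baseline to week 26 by group";
- a test in each arm: "Within each group, paired samples Student *t* tests will be conducted to test differences in MoCA from baseline to week 26";
- a further comparison: "We will also examine a difference in differences analysis within and between groups overall using ANOVA";
- a conditional model: "If data permit, we will use mixed-effects linear models, with time (baseline and week 26) and group (exercise and control) as the fixed effects", with participant as random effect. It takes age, sex, education, disease duration, disease severity and levodopa equivalent dose one at a time.

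The pre-randomisation value of the outcome is not among those covariates. The same section carries the scheme over to the MDS-UPDRS motor score and the four biomarkers. Methods for Additional Analyses repeats it for the exploratory outcomes: "Two-way repeated-measures ANOVA will be conducted to test for differences in each outcome from baseline to week 26 by group", again with paired tests in each arm.

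For MoCA, Table 1 gives the time points as "Screening and 26 weeks", so the pre-value is the screening score. The exclusion criteria remove scores below 23.

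**The concern.** Every pre/post outcome has a measurement taken before randomisation, and it usually predicts the week-26 value. Used as a covariate, it reduces the residual variance and corrects the comparison for any imbalance in that measurement. The planned tests only subtract it.

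This matters more here than in a large trial. Sample Size rests on these efficacy outcomes, only 31 participants are randomised, the sequence is simple, and Allocation Concealment Mechanism says the sequence is open to the enrolling investigator. The stated response to possible imbalance is to compare baseline characteristics, which adjusts nothing. Given an observed imbalance, a change score over-corrects whenever the slope of the week-26 value on the pre-value is below 1.

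The paired tests raise a separate problem. They ask whether each arm moved, not whether the arms differ. A significant result in one arm beside a non-significant one in the other is easily read as benefit, and it arises often when there is none.

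**Working it through.** **Step 1. The two between-group analyses are one test.** With two visits, let D be the week-26 value minus the pre-value. The group-by-time F statistic equals the square of the two-sample t statistic on D, and the difference in differences is the same contrast. On one simulated data set of 31, both routes gave t = −0.1392 and p = 0.8902.

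**Step 2. The plan's own figure.** Sample Size states 80% power for MoCA with 31 participants, two-sided 5%. It gives no SD or correlation, so the figure cannot be reproduced, only inverted. With arms of 16 and 15, df = 29 and non-centrality d/√(1/16 + 1/15) = d/0.3594, 80% power requires d = 1.042 in units of the SD of change. If the cited 1.6 points is the target difference, the implied SD of change is 1.6/1.042 = 1.54. The steps below take d = 1.042 as given.

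**Step 3. What adjustment gains.** With equal variance σ² at both visits and correlation ρ (assumed):

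- change-score variance = 2σ²(1 − ρ);
- ANCOVA residual variance = σ²(1 − ρ²);
- ratio = (1 + ρ)/2.

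ANCOVA power uses non-centrality d·√(2/(1 + ρ))/√(1/n₁ + 1/n₂) with df = n₁ + n₂ − 3. At ρ = 0.5 and 16/15: 1.042 × √(2/1.5) = 1.203; 1.203/0.3594 = 3.35; df = 28; power 89.8%. The lower end of each range below also charges for chance baseline imbalance.

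| ρ (assumed) | variance ratio | planned test, 16/15 | ANCOVA, 16/15 | 31 × ratio |
|---|---|---|---|---|
| 0.3 | 0.65 | 80% | about 93% | 20 |
| 0.5 | 0.75 | 80% | 89–90% | 23 |
| 0.7 | 0.85 | 80% | 85–86% | 26 |
| 0.9 | 0.95 | 80% | 80–82% | 29 |

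The last column is roughly the number of participants that would give ANCOVA the precision 31 give the planned test.

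At the stated 12% attrition, 31 × 0.88 = 27.3, taken as 14/13 completers. The planned test then has 73.9% power, and ANCOVA has 83–85% (ρ = 0.5), 79–80% (0.7) or 74–76% (0.9).

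**Step 4. Truncated screening MoCA.** Excluding scores below 23 reduces the variance of the pre-value. Suppose it halves it (assumed), with ρ the untruncated correlation. The ratio becomes (1 − ρ²)/[0.5(1 − ρ)² + 1 − ρ²]:

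- ρ = 0.5: 0.75/0.875 = 0.857;
- ρ = 0.7: 0.51/0.555 = 0.919.

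At 14/13, with imbalance charged, ANCOVA power is then 78.3% and 75.5%, against 73.9%.

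**Step 5. The paired tests when exercise adds nothing.** Let both arms share a true gain, in SDs of change, with 14/13 completers.

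- Gain 0.5: each paired test is significant with probability 0.410 (n = 14) and 0.382 (n = 13). Exercise only: 0.410 × 0.618 = 0.253, about 25%. Exactly one arm: 0.253 + 0.382 × 0.590 = 0.479, about 48%.
- Gain 0.2: 0.107 and 0.102. Exercise only: 0.107 × 0.898 = 0.096, about 10%. Exactly one arm: about 19%.

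A simulation of 100,000 trials at 16/15 gave 10%, 22%, 26% and 26% for exercise only at gains of 0.2, 0.4, 0.5 and 0.6. The figure was 2.4% with no shared gain and fell back to 5% at a gain of 1.0. The between-group test stayed at 5% throughout.

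**The case against.** The strongest reply is that a valid between-group test is already planned. That stands. The group-by-time test holds its 5% level, running the same test under two names adds no error, and ANCOVA is a gain in efficiency, not the repair of a wrong test. The outcomes are also secondary in a pilot.

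The size is uncertain too. No correlation is given; the gain is close to nothing at ρ = 0.9 and smaller where truncation has cut the pre-value's variance. The 14/13 split is an assumption: the only losses reported are two control participants, and those who stop exercising are asked back at week 26.

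A reader might infer more than the text supports:

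- **That efficacy will be claimed from the paired tests.** The protocol does not say so. Trial Design states the hypothesis as a comparison with control.
- **That regression to the mean favours a false gain in MoCA.** Excluding low screening scores selects high ones, so retest scores drift down. Only retesting or some other shared upward shift would act the other way, and its size is assumed here.
- **That the covariate models are misspecified.** Naming "with time (baseline and week 26) and group (exercise and control) as the fixed effects and participant as the random effect within each model" does not exclude interactions. The stated aim is association with change, and a condensed article may leave such terms to the full plan.
- **That MDS-UPDRS will be a covariate for itself.** This over-reads a statement that the analysis will be similar. The exploratory section defines severity by Hoehn and Yahr stage alone.

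What the reply does not answer is that the pre-value is collected and left unused as a covariate, in a small trial with open allocation, and that p-values are planned for contrasts that are not treatment effects.

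**Conclusion.** The point holds as a worthwhile improvement, not as an error that invalidates the analysis. The planned between-group comparison is sound but unadjusted. Replacing it with ANCOVA would add about 13 points of power at ρ = 0.3, 9–10 at 0.5, 5–6 at 0.7 and 0–2 at 0.9. This assumes equal variances at the two visits and the stated 80% at 16/15. ANCOVA would also correct for imbalance in the measured pre-value, though not for other consequences of unconcealed allocation.

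The within-arm p-values carry a separate risk of misreading: about 10% to 25% of trials with no treatment effect would show significance in the exercise arm alone, given a shared gain of 0.2 to 0.5 SD. That risk belongs to the paired tests, not to the ANOVA.

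**What to change.** For each secondary and exploratory outcome measured before and after, make the deciding analysis an ANCOVA of the week-26 value on group and the pre-randomisation value (the screening score for MoCA). Report the adjusted difference with its 95% CI. Present within-arm changes descriptively, without p-values. Drop the difference-in-differences ANOVA as a separate entry, since it repeats the group-by-time test.

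As a minor clarification, state that the covariate models include covariate-by-time terms and that MDS-UPDRS is not a covariate for its own outcome.

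The cost is wording and one degree of freedom per model. No new data are needed, and the change can be settled before the analysis planned to start in June 2026.

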### Sample Size

We based the sample size calculations on the secondary outcomes of efficacy. Since adherence and feasibility can only be evaluated in the exercise group and are not collected in the control group, it is not possible to calculate power comparing these outcomes between groups. The power and sample size analysis is based on the biomarker of interest, klotho, and the global cognition measure, MoCA. Based on prior studies describing changes in klotho plasma levels with exercise in healthy sedentary adults [33,34], a sample size of 14 participants per group is expected to detect an effect size of 100  pg/mL, considering a type I error of 0.05 with a statistical power of 0.85. Assuming a maximum attrition rate of 12%, we decided to recruit a total of 31 participants (16 participants in the exercise group and 15 in the control group). With respect to cognition, prior endurance exercise and resistance training studies show benefits on cognition at 6 or 12 months [17,35], but Chang et al [36] have shown that endurance exercise for 8 weeks leads to a statistically significant improvement in MoCA (1.6-point increase). Based on our sample size of 31, we will have 80% power with a 2-sided type I error of 0.05 to detect a significant improvement in MoCA.

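### Biomarker comparisons borrow the MoCA change-score methods, by natural reading on the raw concentration scale and without baseline adjustment, which is inefficient with about 29 completers

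*Protocol article*

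**What the plan says.** In the protocol article, Statistical Methods for Primary and Secondary Outcomes sets out the MoCA analysis first: "Two-way repeated-measures ANOVA will be conducted to test for differences in MoCA from baseline to week 26 by group". Paired t tests within each group follow, and then "We will also examine a difference in differences analysis within and between groups overall using ANOVA". Mixed models with time and group as fixed effects are added if the data permit. The covariates listed for those models do not include the baseline value of the outcome under analysis. The biomarkers are then covered in one sentence: "Similar analysis will be performed as above to examine differences in MDS-UPDRS motor score (part III) and circulating biomarkers".

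Two other places indicate the scale. Table 1, under Outcomes (Overview), gives the metric for each biomarker as "Value at time point assessed", with concentration units. Sample Size plans klotho as an additive difference, namely 100 pg/mL: "a sample size of 14 participants per group is expected to detect an effect size of" that amount. The error rate and power attached to this calculation read "considering a type I error of 0.05 with a statistical power of 0.85". The article mentions no logarithm, rank method or distribution check. It does not use the term raw scale either, and it does not exclude a transformation.

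**The concern.** One method serves both a bounded cognitive score and four concentrations that cannot fall below zero. If a marker is right-skewed and exercise changes it by a proportion, people with high baselines have the largest absolute changes. A few of them then dominate the variance of the change scores.

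The Background expects BDNF and klotho to rise with exercise, and CRP and cortisol to fall. Falls are the worse case on the raw scale, because a given log effect makes a smaller absolute difference downwards than upwards.

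Biomarkers are four of the six secondary outcomes in Table 1 and carry the mechanistic aim. Allocation is not concealed and the assessor is not blinded, so a scale chosen after seeing the data would be open to the charge of selection. Separately, a change score uses the baseline value less efficiently than adjustment for it does.

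**Working it through.** **Inputs from the article.** Planned allocation is 16 exercise and 15 control (Sample Size). Two control participants have withdrawn (Recruitment and Retention). I therefore take 16 versus 15 − 2 = 13, or 29 completers. The final split could differ. The two-sided 0.05 level is the one stated for MoCA; no sidedness is stated for klotho.

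**Inputs assumed.** The article gives no SD, CV, skewness or baseline-to-week-26 correlation for any marker. These are varied below.

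**The plan's own klotho figure.** From n = 2(1.960 + 1.036)² SD²/Δ², with n = 14 and Δ = 100 pg/mL, SD = 100 × √(14 / (2 × 8.98)) ≈ 88 pg/mL. The t-test version gives about 85 (standardised effect 1.18). This is back-solved, so 14 per group cannot be checked independently. For attrition, 28 / (1 − 0.12) = 31.8, or 32 against the stated 31, which is immaterial. The planning effect is additive, in concentration units.

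**Equivalence.** With two times and two groups, the time-by-group test in the ANOVA is the two-sample t test on change.

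**Skewed marker, proportional effect.** Simulated lognormal values, 16 versus 13, correlation 0.6 to 0.8. The effect is about 1.08 SD of log change, set to give the log-change t test 80% power. Check: 1.08 × √(16 × 13 / 29) = 2.89, less the critical t of 2.05, is 0.84, and Φ(0.84) = 0.80. Power of the raw-change test:

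| Log-SD | Marker falls | Marker rises |
|---|---|---|
| 0.25 | 72-74% | 80-82% |
| 0.5 | 60-62% | 74-77% |
| 1.0 | 36-37% | 52-58% |

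Repeat runs agree to within one or two points. The asymmetry follows from the ratios: at log-SD 0.5 and correlation 0.7 the effect is a ratio of 1.52 upwards (+52%) but 0.66 downwards (−34%). Under no effect, across log-SD 0.2 to 1.2, the raw test rejects in 3.2 to 5.2% of runs, so it is not anticonservative.

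**Adding the baseline value.** The variance of a change is 2σ²(1 − ρ); after baseline adjustment it is σ²(1 − ρ²). The ratio is (1 + ρ)/2, which is 0.80 at ρ = 0.6 and 0.90 at ρ = 0.8. In simulation, the adjusted log analysis reaches 82-87% for the lognormal cases. For additive effects on normal data, adjusted raw analysis rises from about 80% to the same 82-87%. Under skew with a proportional fall, raw-scale adjustment recovers much of the loss at log-SD 0.25 and 0.5 but only part of it at 1.0.

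**The opposite case: additive effect.** With normal raw data and 80% power for raw change, log-change power (correlation 0.5 to 0.9, both directions) is 74-82% at CV 0.2, 68-80% at CV 0.3 and 59-77% at CV 0.4. With baseline adjustment on both scales, a fall at CV 0.3 to 0.4 has 64-77% power logged against 82-87% raw. With a skewed baseline and an additive rise, log-change power is 69-70% at log-SD 0.5 and 50-56% at 1.0.

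**The case against.** The strongest reply is that analysis scale belongs in a SAP or the full protocol, neither of which is shown, and that raw scale is an inference. That is fair as far as it goes. But the article does not leave the method open. It assigns the MoCA change-score methods to the biomarkers, and Table 1 and the additive klotho effect make the concentration scale the natural reading. A better method can be proposed for one that is stated.

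A second reply is that the harm depends on skew that no part of the article documents. This stands, and it is why the loss is given only as a range.

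A third is that validity is not at risk and that Table 1 already reports median and range, so an outlier would be visible. This also stands, though seeing an outlier does not restore lost power.

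Two stronger readings are tempting. A reader might infer that the raw-scale analysis halves power for the biomarkers generally. The figures do not support that: halving needs a log-SD near 1.0, a proportional effect and a falling marker, or for a rising marker a log-SD near 1.2 with high correlation (39% at 0.9). A reader might also infer that logging costs almost nothing and should apply to all four markers. That fails when effects are additive, and the only biomarker effect the article states, for klotho, is additive.

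**Conclusion.** The point holds as one of efficiency. The stated biomarker analysis compares changes, by natural reading on the concentration scale, and makes no use of the baseline value as a covariate. With about 29 completers, baseline adjustment would raise 80% power to 82-87% at correlations of 0.6 to 0.8, on whichever scale suits the marker. The log scale matters further only for markers that are skewed and change proportionally. There, for a fall, raw change gives up about 6-8 points at log-SD 0.25, 18-20 at 0.5 and 43-44 at 1.0, measured from 80%.

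All of this rests on assumed distributions and correlations. Type I error is not inflated. The outcomes are secondary in a pilot whose primary outcomes are feasibility, adherence and safety, so this is a worthwhile refinement and does not threaten the trial.

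**What to change.** Before analysis starts (planned for June 2026), replace the carry-over sentence with a short statement for the biomarkers:

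- The between-group comparison for each marker is the week-26 value adjusted for its own baseline value.
- The scale is named in advance for each marker. Markers expected to be skewed with proportional change, with CRP and cortisol as candidates, are analysed on the log scale and reported as a ratio of geometric means with a 95% CI.
- Klotho stays on the raw scale, to match the 100 pg/mL planning figure, with the log-scale result as supportive.
- The scale for BDNF is fixed by the same reasoning and recorded.

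The cost is wording only, since baseline samples are already collected. There are two downsides. Effects on logged markers are ratios, so they do not read directly in concentration units. If the true effect is additive with little skew, logging can cost power: little at CV 0.2, but more than 10 points at CV 0.3 to 0.4. For that reason the log scale should be chosen marker by marker.
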